### Efficacy evaluation

The primary outcome, the mean change in MDS-UPDRS Part III score from baseline at 8 weeks between the experimental and control groups will be assessed using an independent t-test. If there is a significant difference in the baseline between the groups, we will use an analysis of covariance. If there is a significant difference in the other baseline variables, we will employ multiple regression analysis. The MDS-UPDRS Part III scores will be assessed at each time point within the confines of a linear mixed effects model with fixed effects for treatment, time, and the interaction of treatment by time, and an unstructured covariance structure for repeated measures within each subject.

The secondary outcomes include the MDS-UPDRS, IPAQ Short Form, PSQ, PDSS, TUG results, GAITRite parameters, fNIRS measurements, number of steps per day, gut microbiome analysis results, and iris connective tissue texture and density. To evaluate the secondary outcomes, we will use analysis of covariance or multiple regression analysis with corrected baseline variables. When the baseline variable is used as a covariate, a PP analysis will be performed without processing missing values.

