### Sample size

The hypothesis of this clinical trial is as follows:

H0 (null hypothesis): μ_t_ = μ_c_H1 (alternative hypothesis): μ_t_ ≠ μ_c_

μ_t_ denotes the average change in MDS-UDPRS Part III score from baseline to 8 weeks in the treatment group (MARS-PD treatment), and μ_c_ denotes the average change in MDS-UDPRS Part III score from baseline to 8 weeks in the control group (usual care). The experimental and control groups will be recruited in a one-to-one ratio.

For the determination of the sample size, we referenced a previous study that closely resembled our current investigation in terms of research design, treatment period, treatment method, number of participant visits, and outcome variables [21]. In the study conducted by Hackney and Earhart, a total of 33 patients diagnosed with PD were enrolled, with 17 participants in the exercise (Tai Chi) group and 16 in the control (no intervention) group. The treatment period lasted 10–13 weeks, with a total of 20 treatment sessions. One of their outcome variables was the UPDRS motor subscale (Part III). The observed average change in UPDRS Part III scores for the treatment and control groups were -1.5 ± 6.6 and 4.3 ± 5.6, respectively. The mean difference in effect between the Tai Chi group and control group was calculated as 5.8, with a pooled standard deviation was 6.1. These parameters from the previous study served as a basis for informing the sample size calculation in our current research design.

We used a conservative value of 5 for the mean difference of the effect and 6.5 for the standard deviation to calculate the number of test subjects to confirm the effect of the experimental group compared to the control group in this study. According to Shulman et al. [22] and Sánchez-Ferro et al., [23] the minimal clinically important difference (MCID) for UPDRS Part III is 2.3 and 5, respectively. In the meantime, Horváth et al. [24] estimated that the MCID for MDS-UPDRS Part III is between 2.3 and 2.7 points. Therefore, the proposed mean difference of the effect of 5 is equal to or greater than the MCID that was previously reported by the studies. Substituting this into the calculation formula [25] results in approximately 36 people per group as shown below. Considering the dropout rate of 20%, a total of 88 clinical trial subjects, 44 per group, are required. The criteria for dropout is specified in the protocol (S2 Appendix).

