$$\frac{2*{\left(Z_{1-\frac{\alpha }{2}}+Z_{1-\beta }\right)}^{2}*\sigma^{2}}{\mu_{t}-\mu_{c}}=\frac{2{\left(1.96+1.28\right)}^{2}*6.5^{2}}{5^{2}}\sim 36$$

Where α (two-tailed test significance level) = 0.05; β (type 2 error) = 0.1; 1-β (power) = 90%.

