### Statistical analysis

To calculate compliance for each subject, we will use the following formula:

$$Compliance\left(\%\right)=\frac{number\;of\;interventions\;actually\;conducted}{number\;of\;interventions\;originally\;planned}$$

Throughout the trial, it is imperative that compliance (%) remains at or above 75%. Subjects falling below this threshold will be considered insufficiently compliant and subsequently excluded from the per-protocol (PP) analysis. The efficacy analysis will be primarily assessed based on the full analysis set (FAS) principle, followed by the PP principle for primary and secondary outcomes.

The FAS analysis will be carried out on cases that meet the principle of intention-to-treat (ITT). The FAS analysis will exclude cases falling into the following categories: (1) subjects not meeting the main eligibility criteria, (2) those not receiving the intervention specified in the protocol, and (3) individuals who were never evaluated after randomization with no collectable data.

On the other hand, the PP analysis will be carried out on cases that have successfully completed the entire trial process without any protocol violations. The PP analysis will exclude cases meeting any of the following criteria: (1) subjects dropping out during the intervention period, (2) violation of eligibility criteria, (3) compliance falling below 75%, and (4) any other serious violations of the clinical trial protocol.

By adopting this approach, we aim to evaluate the results conservatively, considering PD’s natural tendency to worsen over time. Statistical analysis will be conducted using the two-tailed test method, and a p-value of < .05 will be deemed statistically significant. In the event of missing values, appropriate imputation methods will be employed based on the underlying cause.

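### Baseline significance tests choose the primary model; a single baseline-adjusted ANCOVA fixed in advance would be more precise and would cost only wording

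*Protocol article*

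**What the plan says.** All of this is in the protocol article, section Efficacy evaluation, unless noted.

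- **Default.** The change in MDS-UPDRS Part III from baseline to week 8 "between the experimental and control groups will be assessed using an independent t-test".
- **First switch.** "If there is a significant difference in the baseline between the groups, we will use an analysis of covariance".
- **Second switch.** "If there is a significant difference in the other baseline variables, we will employ multiple regression analysis". The variables are not listed. Nothing says what happens if both conditions are met, or whether the regression would keep the baseline Part III score.
- **Mixed model.** Part III at each time point is also to be modelled with "fixed effects for treatment, time, and the interaction of treatment by time, and an unstructured covariance structure". No baseline covariate is among the listed terms.
- **Secondary outcomes.** These are to be analysed by ANCOVA or regression with baseline variables outright, with no significance test first.
- **Significance level.** The section Statistical analysis says that "a p-value of < .05 will be deemed statistically significant". No separate level is given for the baseline comparisons.

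**The concern.** In a randomised trial any baseline difference is due to chance, so a significance test of it answers no useful question. How far an imbalance distorts the result depends on its size and on how strongly the variable predicts the outcome, not on whether its p-value falls below 0.05. Baseline Part III is certain to predict change in Part III unless the slope of week 8 on baseline is exactly 1.

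Three things are at stake:

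- The model behind the only primary result is settled by the data.
- In trials with a sizeable imbalance that just misses significance, the t-test estimate is shifted by regression to the mean.
- Precision from a covariate that the trial already measures is given up.

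A later analysis plan that follows the stated rule would inherit all three.

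**Working it through.** **The plan's own figure.** The section Sample size gives "We used a conservative value of 5 for the mean difference of the effect and 6.5 for the standard deviation" and "α (two-tailed test significance level) = 0.05; β (type 2 error) = 0.1; 1-β (power) = 90"%. Then n per group = 2 × (1.96 + 1.28)² × 6.5² / 5² = 35.48, rounded up to 36, as stated. Normal-approximation power at 36 per group is 0.904. With 44 randomised per group and 20% dropout, 44 × 0.8 = 35.2, so about 35 complete.

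**How often the baseline-score switch fires.** At 0.05 under randomisation it fires in 5% of trials. That switch leaves the t-test in place in the other 95%.

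**What ANCOVA gains.** Let ρ be the baseline-to-week-8 correlation, which the document does not give, and assume equal SDs σ at both times.

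- Variance of change = 2σ²(1 − ρ).
- Residual variance after adjusting for baseline = σ²(1 − ρ²) = variance of change × (1 + ρ)/2.
- With SD of change 6.5 and the pilot baseline SD of 11.78 (section Objectives), ρ = 1 − 6.5² / (2 × 11.78²) = 1 − 42.25/277.54 = 0.85.
- At 36 per group, normal-approximation power with ANCOVA is 0.965, 0.943, 0.924 and 0.918 at ρ = 0.5, 0.7, 0.85 and 0.9. The n per group for 90% power falls from 36 to 27, 31, 33 and 34.

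**Simulated power, 35 per group, difference 5, SD of change 6.5.** The rule here is the t-test, replaced by ANCOVA if baseline Part III differs at 0.05.

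| ρ (assumed) | Rule, % | Always ANCOVA, % | Loss, points |
|---|---|---|---|
| 0.5 | 89.6 | 95.3 | 5.7 |
| 0.7 | 89.1 | 92.7 | 3.6 |
| 0.8 | 88.9 | 91.2 | 2.3 |
| 0.85 | 89.0 | 90.7 | 1.7 |
| 0.9 | 89.0 | 89.9 | 0.9 |

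Overall type I error of the rule in these runs was 4.5 to 5.0%. Among trials with baseline p between 0.05 and 0.20 (about 15% of trials), the t-test rejected a true null 9.4% of the time at ρ = 0.5, falling to 5.9% at ρ = 0.9. ANCOVA stayed at about 5%.

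**Separate simulation under the null, 36 per group, 200,000 trials per setting.** The last three columns cover the roughly 9% of trials whose baseline t statistic exceeds 1.5 in absolute value without being significant.

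| ρ (assumed) | Rule, overall type I error, % | t-test rejects, % | ANCOVA rejects, % | Mean spurious difference, points |
|---|---|---|---|---|
| 0.5 | 4.3 | 9.8 | 4.7 | 1.3 |
| 0.7 | 4.7 | 8.3 | 5.0 | 1.0 |
| 0.85 | 4.9 | 6.8 | 4.8 | 0.7 |
| 0.9 | 4.9 | 6.1 | 5.0 | 0.6 |

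Power in the same setting was 90.5, 90.0, 89.8 and 89.6% for the rule, against 95.8, 93.3, 91.4 and 90.6% for ANCOVA, a loss of 5.3 down to 1.0 points.

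**The other-variables switch.** With k independent variables each tested at 0.05, the chance that at least one fires is 1 − 0.95^k: 23% for k = 5, 40% for k = 10 and 51% for k = 14. The protocol article gives no k, so these are illustrations. The error rate of the regression branch was not simulated.

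**The case against.** The best defence is that the stated test works. Over all randomisations the t-test on change is unbiased, it matches the test behind the sample size, and the baseline-score rule keeps both nominal type I error and close to the planned 90% power. All of that stands, and it limits how serious the point is.

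The conditional error rates also have a counterpart. In trials with baseline p above 0.20 (about 80% of trials), the t-test rejects a true null 3.5 to 4.5% of the time, which is why the overall rate is not raised.

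A reader might infer four stronger things that the document does not support:

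- **That chance imbalance in Part III goes uncorrected.** A change score subtracts baseline. What remains is regression to the mean, a fraction (1 − ρ) of the gap under equal SDs.
- **That the estimate could shift by as much as 2.6 points.** The largest non-significant gap at 44 per group is t(0.975, 86) × 11.78 × √(2/44) = 4.99 points. A shift of 2.6 needs a slope of change on baseline of 5.54/11.78 − 1 = −0.53. That means a correlation at or near 1, with the SD shrinkage of a treated-only pilot group applied to both arms. Nothing shows such shrinkage under usual care. Under equal SDs and ρ = 0.85 the shift at that edge is 4.99 × 0.152 = 0.76 points.
- **That the analyst may pick among four models.** The text names a default and two switches. The mixed model is described for scores at each time point and is not offered as a replacement for the primary test.
- **That regression will be triggered in 40% of trials.** That figure holds only for ten independent tested variables, a number that the document does not give.

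None of this answers the core point. The document itself states the data-dependent choice, and the secondary outcomes already get baseline adjustment without a test.

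**Conclusion.** The concern holds as a moderate one. The primary model depends on baseline significance tests, the second trigger is undefined because its variables are not listed, and the default ignores a measured prognostic covariate.

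The loss against always using ANCOVA is about 6 points of power at ρ = 0.5, under 2 at ρ = 0.85 and about 1 at ρ = 0.9. The lower end is the better supported, because ρ = 0.5 would imply a baseline SD of only 6.5 against 11.78 in the pilot. With a near-significant imbalance, false rejection by the t-test is about 9 down to 6%.

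These sizes rest on an assumed ρ, equal SDs at both times, normal data and baseline tests at 0.05. The statement on overall type I error covers the baseline-score switch only. The trial is not underpowered or invalid on this account. The point should be fixed because the gain is free and the confirmatory model ought to be settled beforehand.

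**What to change.** In the section Efficacy evaluation, delete both conditional sentences and name one primary analysis: ANCOVA of the week 8 change in MDS-UPDRS Part III on treatment arm, with baseline Part III as covariate, in the FAS, whatever the baseline comparison shows. Using the week 8 score in place of the change gives the same treatment effect once baseline is in the model.

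If other covariates are wanted, list them now and include them unconditionally. Label the unadjusted t-test and the mixed model as supportive. Baseline variables may be described by arm, but significance tests of them should not choose the model.

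The secondary-outcome paragraph ties use of a baseline covariate to a per-protocol analysis without handling of missing values. State that this does not apply to the primary ANCOVA.

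The cost is wording only, through a protocol amendment before unblinding. No extra data or participants are needed, and the 88 planned can stand.

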### Economic evaluation

To confirm the cost-effectiveness of the intervention in this clinical trial versus existing treatment (usual care), an economic evaluation will be conducted concurrently with the clinical trial. The primary economic endpoint of the study is cost per Quality Adjusted Life Years (QALY) gained. To calculate QALY, quality of life will be derived from the EuroQol five dimensions questionnaire (EQ-5D) using area under the curve method [26]. The secondary economic endpoint of the study is cost per the EuroQol Visual Analogue Scale (EQ-VAS). The cost will be determined as follows: (1) the treatment cost incurred in relation to the clinical trial will be calculated by combining the number of treatments and the unit cost, and (2) the treatment cost incurred within the clinical trial institution will be recorded by the researcher by examining the EMR after unblinding.

FAS analysis will be used for economic evaluation, while PP analysis will be used to test the sensitivity of the analysis results to missing values. The primary evaluation period will be 12 weeks, which corresponds to the study’s total follow-up period. If an evaluation needs to be done after 12 weeks, the costs and effects will be extrapolated and estimated using a regression model, or a secondary analysis, such as decision modeling analysis. If the total analysis period (time horizon) exceeds 12 months, the cost unit will be unified into Korean currency (won) in 2021, and a 5% discount rate will be applied based on the Health Insurance Review and Assessment Service economic evaluation guidelines.

The findings of the economic analysis will be presented as follows: (1) a table displaying analysis results, including the incremental cost-effectiveness ratio, (2) a cost-effectiveness plane containing confidence intervals confirmed by non-parametric methods, (3) the Cost Effectiveness Acceptability Curve (CEAC), which measures cost-effectiveness sensitivity to changes in national thresholds, and (4) a graph displaying the value of information analysis results, which can be used to estimate the value of information for the target population group.

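### The rule for baseline-adjusted analyses (per-protocol, missing values left unhandled) contradicts the plan's FAS-first rule with imputation and, as worded, governs most secondary outcomes

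*Protocol article*

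**What the plan says.** The Statistical analysis section sets a general rule: "The efficacy analysis will be primarily assessed based on the full analysis set (FAS) principle, followed by the PP principle for primary and secondary outcomes". On missing data it says: "In the event of missing values, appropriate imputation methods will be employed based on the underlying cause". PP excludes patients who drop out during the intervention period, violate eligibility, fall below 75% compliance, or seriously breach the protocol in another way. Compliance is the number of sessions delivered divided by the number planned.

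The Efficacy evaluation section gives the methods. For the primary outcome, the change "between the experimental and control groups will be assessed using an independent t-test". The first exception is: "If there is a significant difference in the baseline between the groups, we will use an analysis of covariance". Significant differences in other baseline variables lead to multiple regression. Part III at each time point also gets a linear mixed model with treatment, time and their interaction as fixed effects.

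For the rest: "To evaluate the secondary outcomes, we will use analysis of covariance or multiple regression analysis with corrected baseline variables". The next sentence, which closes the secondary-outcome paragraph, is "When the baseline variable is used as a covariate, a PP analysis will be performed without processing missing values".

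In the Economic evaluation section FAS is the main set, and "PP analysis will be used to test the sensitivity of the analysis results to missing values".

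**The concern.** Two rules are stated for the same analyses, and they differ on who is analysed and on what happens to missing values. Two analysts could each follow the article and report different headline populations for most secondary outcomes.

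The choice matters because a PP complete-case comparison is between selected patients, not between the groups as allocated. Participants and intervention staff know the allocation, so attendance and dropout can depend on it. Blinding the evaluation staff protects the measurement, but not the choice of who remains in the analysis. The 75% compliance exclusion also works in one arm only, because controls have no planned sessions to miss.

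**Working it through.** **1. The two rules side by side**

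| | Statistical analysis section | Efficacy evaluation section, baseline as covariate |
|---|---|---|
| Set | FAS first, PP second | PP |
| Missing values | Imputed according to cause | Not handled |
| Scope | Primary and secondary outcomes | Any analysis with the baseline variable as covariate, stated in the secondary-outcome paragraph |

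**2. Which outcomes are reached.** Table 2 has twelve secondary rows.
- Part III at 4 and 12 weeks (one row) is covered by the mixed model, which lists no separate baseline covariate. Not reached.
- The two iris rows are measured at baseline only, so there is no follow-up to lose. Not reached.
- The remaining 12 − 1 − 2 = 9 rows have follow-up and are assigned to baseline-adjusted ANCOVA or regression. Reached on the plain wording.
- The default primary t-test has no covariate. Not reached.
- A primary ANCOVA triggered by a baseline difference is reached only if the sentence is read beyond its paragraph. In that case a baseline test at the 0.05 level selects the primary population. Under sound randomisation this happens about 5% of the time for baseline Part III.

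**3. What PP removes.** The threshold is 0.75 × 16 = 12 sessions, so patients with fewer than 12 are excluded. For controls the planned number is zero and the ratio is undefined. The exclusion can therefore fall only on MARS-PD.

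**4. The plan's own figure.** With difference 5, SD 6.5, two-sided α 0.05 and power 90% (Sample size section): 2 × (1.96 + 1.28)² × 6.5² / 5² = 35.48, or 36 per group. This reproduces. For 20% dropout, 36 × 1.2 = 43.2 gives the stated 44. Dividing by 0.8 gives 45, a difference that does not matter here.

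**5. Power cost.** Power = Φ(5 / (6.5 × √(2/n)) − 1.96).
- n = 44 per arm: SE 1.386, 5/SE = 3.608, power 0.950. This is a ceiling, because it assumes that no one is excluded from the FAS and that no information is lost to missing data.
- n = 35 per arm (44 × 0.8 = 35.2): SE 1.554, 5/SE = 3.218, power 0.896.

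These are Part III planning figures. The article gives no effect sizes for the secondary outcomes.

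**6. Bias, as an illustration only.** Suppose a fraction f of an arm is removed and those patients average g points worse than the patients kept. The arm's mean then shifts by f × g, and the net bias is f_MARS × g_MARS − f_control × g_control. Equal selection in both arms cancels. The documents give neither g nor the arm-specific f. Assume removal from MARS-PD only, no true effect, SD 6.5, and SE = 6.5 × √(1/44 + 1/(44(1 − f))):

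| f | g | Shift f × g | Two-sided error at nominal 5% |
|---|---|---|---|
| 0.10 | 2 | 0.20 | 5.2% |
| 0.20 | 4 | 0.80 | 8.5% |
| 0.30 | 6.5 | 1.95 | 24.8% |

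The table is on the Part III scale. It shows how the mechanism works and is not an estimate for this trial.

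**The case against.** The best defence is that the two sections can be reconciled. The general rule already promises a PP run after the FAS run, and the disputed sentence does not say that PP replaces FAS. It could mean only that the PP run of the adjusted models uses complete cases. The Economic evaluation section, with FAS as main set and PP as check, fits that pattern. This reading is possible, and it is why the point is a contradiction to be resolved and not a settled change of analysis set. It remains the weaker reading. The sentence does not mark PP as additional or supportive, no FAS version of the adjusted analysis is named, and the condition on using a covariate would be unnecessary if only the routine PP run were meant.

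A reader might infer more than the documents support:
- *Every secondary outcome loses its FAS analysis.* No: Part III at 4 and 12 weeks has the mixed model, and the iris measures have no follow-up.
- *The primary outcome is moved to PP.* Not by default. The sentence stands in the secondary-outcome paragraph, so applying it to a triggered adjusted primary analysis is an inference from its general wording.
- *The economic evaluation repeats the error.* It does not, because FAS is its main set. The weaker point there is that PP is a poor check on missing data.
- *The bias has a known size.* It does not. The planned 20% dropout applies to both arms, early dropouts overlap with patients under 12 sessions, and no outcome gap is given.
- *The plan's claim to be conservative is reversed.* That remark covers the whole FAS-then-PP scheme, not PP alone.

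It is also fair to say that the article's FAS itself excludes ineligible patients, those not given the intervention, and those never evaluated. Moving to it improves the comparison but does not fully restore the randomised groups.

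**Conclusion.** The concern holds as a contradiction between the Statistical analysis and Efficacy evaluation sections, on both analysis set and missing data. On the plain wording it affects nine of the twelve secondary rows in Table 2. The default primary t-test and the Part III mixed model are unaffected. If the sentence is also taken to cover the primary outcome, a significant baseline test would move that outcome from FAS to PP, and the wording should rule this out.

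The loss of power is modest: at most 0.950 to 0.896 on the primary's planning figures with 20% loss in each arm. The main risk is selection. Bias in favour of MARS-PD is plausible because the compliance exclusion can apply only to that arm, but this requires that excluded patients would have done worse, and the documents give nothing from which to size it. The conflict should be resolved before unblinding.

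**What to change.** Replace the disputed sentence with a statement along these lines: all baseline-adjusted analyses of primary and secondary outcomes, including any adjusted primary analysis, are run first in the FAS; missing follow-up is handled by a mixed model or by multiple imputation; the PP complete-case analysis is supportive only. For the microbiome, which has a single follow-up at 8 weeks, multiple imputation is the natural choice of the two.

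Lesser point, Economic evaluation section: PP removes non-compliers as well as dropouts, so it mixes adherence with missingness and never varies the missing-data assumption. Use multiple imputation under varied assumptions as the missing-data sensitivity check, and keep PP as a separate adherence analysis if it is wanted.

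The cost is plan wording and a modest amount of extra programming. The sample size and data collection do not change.
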